## Abstract

**Background:** Victims of physical/sexual violence or sexual abuse commonly experience defense responses that result in feelings of guilt and shame. Although trauma-focused interventions are effective in treating post-traumatic stress disorder symptoms, the presence of trauma-related shame and guilt can potentially hinder the process of disclosure during treatment, thus diminishing their overall effectiveness. It is hypothesized that providing psychoeducation about common defense responses will reduce feelings of shame and guilt, thereby increasing receptivity to trauma-focused treatment.

**Objective:** This paper describes the rationale, study design, and methods of the BLAME-LESS study. The effects of a brief online psychoeducation program will be compared with a waiting-list control group. The intervention aims to reduce feelings of trauma-related shame and guilt that adolescents experience regarding their own defense responses during and after physical/sexual violence or sexual abuse.

**Methods:** Adolescents (12 – 18 years old) with a history of physical/sexual violence or sexual abuse who suffer from trauma-related feelings of shame and guilt can participate in the study. The study follows a two-arm RCT that includes 34 participants. The primary outcomes includes trauma-related feelings of shame and guilt. The secondary outcomes includes PTSD symptoms, anxiety and depression symptoms, traumatic cognitions, readiness to disclose details of memories of the trauma, and motivation to engage in trauma-focused therapy. Assessments take place after screening, at baseline, two weeks after allocation to the intervention or waiting-list, and, only for the waiting-list participants, seven weeks after allocation to the intervention.

**Conclusions:** There is a need for treatment approaches that target trauma-related feelings of shame and guilt. A recently developed brief online psychoeducation program on defense responses during and after trauma offers victims of physical/sexual violence or sexual abuse a free and accessible way to obtain reliable and valid information. The proposed RCT will evaluate the effectiveness of this online psychoeducation program.

**Trial Registration:** Request is pending.

## Background

1.

A meta-analysis (Alisic et al., 2014) indicate that 16% of children exposed to trauma develop post-traumatic stress disorder (PTSD). Among the different types of trauma, children who experience interpersonal trauma are at a higher risk of developing PTSD symptoms (Alisic et al., 2014; Nöthling et al., 2017). Interpersonal trauma refers to the experience of harm or distress within the context of a relationship or interaction with others, typically stemming from deliberate actions such as abuse or violence. Interpersonal trauma can have profound and lasting effects on an individual’s mental, emotional, and physical well-being. Importantly, individuals who have experienced interpersonal trauma often exhibit feelings of trauma-related shame and guilt (Holliday et al., 2018; MacGinley et al., 2019).

The experience of emotions, such as trauma-related shame and guilt, is often rooted in a child’s reactions during or after a traumatic event (Ehlers et al., 2003; Kernan & Sullins, 2022). These reactions can encompass feelings of self-blame, inadequacy, and a sense of responsibility for the occurrence of trauma. Individuals may internalize negative beliefs about themselves, attributing the traumatic event to their actions or perceived shortcomings. These reactions can be influenced by negative self-evaluations based on personal beliefs or societal expectations (Gilbert, 2019). These negative reactions might be explained by the Just World Theory (Lerner, 1980), in which people tend to see the world as fair, believing that good actions lead to positive outcomes and bad actions to negatives. This belief offers predictability and control, and individuals, including family and friends, may attribute blame to victims for maintaining their own beliefs. For instance, cases of sexual trauma commonly involve victim blaming, whereby the victim is held accountable for the outcome (van der Bruggen & Grubb, 2014). Victim blaming can manifest in various ways, such as attributing blame to the victim based on their clothing, suggesting that they contributed to the abuse, asserting that they did not explicitly say ‘no’, or failing to establish other clear boundaries. Consequently, victims may also engage in self-blame, assuming responsibility for actions that may have contributed to interpersonal trauma. However, it is worth noting that victim blaming tends to be more prevalent when victims do not actively defend themselves (e.g. fight) (Gravelin et al., 2018), which is often the case for interpersonal trauma.

In life-threatening situations, defense responses, such as fight or flight, encompass survival-based reflexive and automatic behavioural and physical reactions. In addition to the commonly known ‘fight-flight’ responses, individuals may exhibit several other defense responses during traumatic events. For instance, victims of physical/sexual violence or sexual abuse often experience a state of ‘freezing’, also known as ‘tonic immobility’ (TI) (Kalaf et al., 2017). Research has shown that victims frequently report TI as a perceived defense response during instances of sexual or physical violence (Hagenaars, 2016; Möller et al., 2017), and its presence during interpersonal trauma is linked to the severity of PTSD symptoms following trauma (Coimbra et al., 2023). Furthermore, according to Bracha (2004), the ‘fright’ and ‘faint’ responses are also considered defense responses. Kozlowska et al. (2015) identified various common defense responses as part of the defense cascade, including arousal, freezing, fight or flight, tonic immobility, collapsed immobility (threat-induced fainting), and quiescent immobility (a state of quiescence that promotes rest and healing). A recent literature review by Van Minnen (2017) addressed several defense responses specific to (repeated) interpersonal trauma, such as arousal, freezing, flight, fight, appeasement behaviour (including reconciliation and non-disclosure), and tonic immobility. These more unknown defense responses can be confusing, particularly in younger victims, and may lead to self-attributing questions. This is particularly the case regarding appeasement behaviour (questions like ‘Why did I go back to the perpetrator?’ ‘Why did I continue being nice to him?’ ‘Why did I not tell anyone?’) and tonic immobility (e.g. ‘Why did I not scream or fight?’).

The concept of defense cascade, a continuum of innate, hard-wired, automatically activated defense behaviours, and related defense reactions, is not well known among trauma victims or their social environment (Kozlowska et al., 2015). Lack of knowledge and misunderstanding of one’s defense responses can result in negative evaluations of these responses (Gilbert, 2019) and severe self-blame, as expressed by increased feelings of shame, guilt, dysfunctional post-traumatic cognition, and other PTSD-related symptoms. To illustrate, children and adolescents (5–16 years) who have been victims of interpersonal violence and who have feelings of guilt about whether or not they acted ‘right’ during the traumatic event experience more PTSD symptoms (Kletter et al., 2009). Moreover, negative cognitions and emotions, such as self-blame, shame, and guilt, can hinder the effectiveness of trauma-focused treatment (Øktedalen et al., 2015). Individuals who experience these feelings may avoid engaging in trauma-focused therapy altogether or withhold full disclosure of their reactions during and after a traumatic event. This is particularly evident among individuals aged 12–17 years, as they are less likely to disclose instances of sexual abuse than older individuals (Bicanic et al., 2015). While interventions targeting posttraumatic stress symptoms in children and adolescents have shown efficacy (John-Baptiste Bastien et al., 2020; Thielemann et al., 2022), trauma-focused interventions appear to be less effective when individuals experience pretreatment shame and guilt related to trauma (Øktedalen et al., 2015). This finding suggests that shame and guilt may impede recovery from trauma-related health problems. Notably, studies have demonstrated that changes in posttraumatic cognitions predict changes in posttraumatic stress symptoms (Schumm et al., 2015), and successful PTSD treatment is partly mediated by a reduction in the severity of trauma-related cognitions (Brown et al., 2018). Thus, it is crucial to implement specific interventions that address trauma-related shame and guilt prior to initiating trauma treatment, with psychoeducation being one such intervention that can encourage participation in therapy and facilitate disclosure, ultimately leading to improved outcomes.

Psychoeducation has been identified as a commonly used technique in the treatment of trauma-related symptoms (Kooij et al., 2022). Increased knowledge of reactions during sexual abuse has been associated with reduced victim blaming in adults, as measured post-intervention (Grandgenett et al., 2022). Additionally, a recently developed psychoeducation programme aimed at increasing knowledge about sexual and domestic violence, including common reactions to sexual abuse, resulted in fewer PTSD symptoms among adults immediately after the intervention (Laun, 2015). Similarly, in a controlled study involving adolescent victims of bullying, a short psychoeducation programme (4–6 h) led to immediate pre–post effects in decreasing self-blame and increased disclosure (Boulton & Boulton, 2017). Building on these findings, we hypothesized that providing psychoeducation about common defense responses as part of the defense cascade could contribute to a reduction in feelings of shame and guilt. Notably, to our knowledge, there are currently no standalone psychoeducation programmes specifically targeting the reduction of trauma-related shame and guilt related to one’s own defense responses during and after physical/sexual violence or sexual abuse. Consequently, we developed a brief online psychoeducation programme called BLAME-LESS (in Dutch: On(t)schuldig) (Stutterheim et al., 2022) that aims to educate adolescents about common defense reactions specific to (repeated) physical/sexual violence or sexual abuse, including arousal, freezing, flight, fight, appeasement behaviour (including reconciliation and non-disclosure), and tonic immobility (see Table 1 for a more detailed overview of the addressed defense reactions). We included podcasts, written information, and explanatory animations. Online interventions for trauma-related problems, as well as mental health problems in general, have become increasingly common and effective (Zhou et al., 2021), further enhancing the accessibility of psychoeducation programmes.

**Table 1. T0001:** Overview of the intervention.

Module	Main components
Module 1:	**Written information**
	*Content*
	Written information on the webpage explaining several defense responses that can occur during and after physical/sexual violence or sexual abuse; (1) during: arousal, freezing, flight, fight, appeasement behaviour (including reconciliation and secrecy), and tonic immobility. (2) after: attentional threat bias, vigilance, avoidance, hostility and embitterment, revictimization, shame, blame and nondisclosure, and freeze, numbing and amnesia. The written information is accompanied by illustrative case reports
	*Effort*
	The expectation is that module 1 will require approximately 60 min of time investment by the participant
Module 2:	**Animations**
	*Content*
	One visualized animation with voice-over about the defense cascade
	Two in-depth explanatory animations with voice-over of the most common defense responses: freeze/tonic immobility and appeasement behaviour
	*Effort*
	The expectation is that module 2 will require approximately 15 min of time investment by the participant
Module 3:	**Podcasts**
	*Content*
	Two in-depth interviews with trauma-experts about the defense cascade and how defense responses are unintentional, involuntary, and automatic responses with the purposes to survive life threating situations
	Three in-depth interviews about the defense cascade with two female adolescent survivors (age 18 and 20) of violence and sexual abuse
	*Effort*
	The expectation is that module 2 will require approximately 30 min of time investment by the participant

The primary objective of the BLAME-LESS study is to examine the effectiveness of an online psychoeducation programme, BLAME-LESS, compared to a waiting-list control group of adolescents (12–18 years), who experienced physical/sexual violence or sexual abuse, in reducing trauma-related feelings of shame and guilt. The second objective of the research is to examine the effects of the intervention on PTSD symptoms, anxiety and depression symptoms, and post-traumatic cognitions, including self-blame. Finally, by learning about common defense responses, we hypothesized that the online psychoeducational programme would increase adolescents’ willingness to disclose their trauma history and enhance their readiness and motivation to participate in trauma-focused treatment.

## Methods

2.

### Study design

2.1.

An RCT will be conducted to study the effectiveness of a brief online psychoeducation programme called BLAME-LESS. The psychoeducation programme is an eHealth module with no active therapist involvement. Participants will be randomized into either the intervention group or the waiting-list control group. If allocated to the intervention group, participants will have direct access to the online intervention for two weeks after allocation. When a participant is assigned to the waiting-list control group, he or she has a two-week waiting period, after which the participant will have access to the intervention. Assessments take place after screening (T0), at baseline (T1), and two weeks after allocation (T2). Participants in the waiting-list group will also be assessed two weeks after they have gained access to the intervention (T3). Figure 1 provides an overview of the study design. The study protocol has been approved by the Medical Ethical Committee Oost-Nederland in the Netherlands (NL82795.091.22).

**Figure 1. F0001:**
[figure not shown]
Study design.

### Research setting

2.2.

The study was funded by Fonds Slachtofferhulp (grant number ‘20.08.18 deel 2’) and will be coordinated and executed at the Karakter Academic Centre for Child and Adolescent Psychiatry in the Netherlands, which includes 13 outpatient departments in four regions of the Netherlands.

### Participants

2.3.

Participants are adolescents between the ages of 12 and 18 who are referred to one of the outpatient departments. Participants may be referred by a general practitioner, pediatrician, or another youth care professional. Reasons for referral can vary, ranging from specific referrals for the current research project to general referrals for diagnostic psychiatric assessment and/or treatment. In all cases, participants and both parents (or legal guardians) provided consent for referral.

All participants meet the following criteria: (1) the participant experienced one or more traumatic life events, including physical/sexual violence or sexual abuse as indicated by the CTSQ; (2) the participant reported one or more trauma related feelings of guilt and/or shame on the CERQ (subscale ‘blaming oneself’: items 1 and/or 10 and/or 19 and/or 28), and these feelings are related to their defensive responses as indicated by a score of >4 on the VAS-scale; (3) the participant being fluent in written and spoken Dutch; (4) the participant is motivated and available for a period of seven weeks to engage in the study, including the psychoeducation programme BLAME-LESS, and commit to the assessments; and (5) The participant has the option to participate in the intervention on their own computer or smartphone. Exclusion criteria are: (1) acute suicidal behaviour or suicidal ideations requiring immediate hospitalization; (2) has already read the book that this programme is based upon: ‘Paralyzed with Fear’ (In Dutch: Verlamd van Angst by Agnes Van Minnen, 2017) or has been intensively informed otherwise in the past 12 months by a psychologist about common defense responses during and after trauma; (3) Cognitive Impairments (IQ < 70); (4) a brother or sister in the present study to avoid the potential transference of treatment effects (contamination bias) if siblings are randomized in different conditions (Magill et al., 2019); and (5) the adolescent is already involved in trauma-focused treatment.

### Procedure

2.4.

The first step of the procedure is to screen all adolescents referred to one of the outpatient departments. Part of the referral procedure is to complete an enrolment questionnaire. The enrolment questionnaire is a standard component of the clinical procedure that all parents (or legal guardians) and adolescents fill in, and this procedure is also used to check for inclusion and exclusion criteria for various research projects. The research assistant will check the following screening tools within the enrolment questionnaire: Child Trauma Screening Questionnaire (CTSQ), Cognitive Emotion Regulation Questionnaire (CERQ), and Visual Analog Scale (VAS). The research assistant will then check whether the inclusion and exclusion criteria are met. Part of the enrolment questionnaire is also that both the adolescent and the parents or legal guardians (for adolescents between the age of 12–16) can indicate if they give permission to be contacted by the researcher. If the adolescent (or the parents/legal guardians) declined, the data obtained from the enrolment questionnaire are solely utilized by the intake professional at the commencement of the treatment process.

When the screening data indicate that an adolescent qualifies for the study, and the adolescent and both parents or legal guardians agree (only necessary for adolescents age 12–16) to be approached for research purposes, contact will be initiated by a research assistant to discuss participation in the study. Throughout all instances, participants are explicitly apprised of the voluntary nature of completing the screening questionnaires for research purposes. Furthermore, the participant is informed in advance that if they are between 12 and 16 years old and consent to being contacted to discuss participation in scientific research, their parents or legal guardians will also be informed. Apart from being a legal requirement, this also aims to prevent participants from disclosing events that they may or may not want to inform their parents about. This minimizes the risk of parents being newly informed about their child’s victimization by the research team. It should also be acknowledged that this approach may potentially result in limited reach to a subset of adolescents, primarily because of constraints stemming from their current circumstances that prevent full disclosure. Conversely, individuals aged 16 years and older are governed by distinct legal and regulatory regulations. Within our jurisdiction, these participants hold the autonomy to independently determine their participation in scientific research. Commencing the procedural sequence, we ascertained their preferred mode of contact and we will not inform their parents or legal guardians.

When meeting the inclusion criteria, the participants will receive a letter with information about the intervention, study, and informed consent form. Parents (or legal guardians) from participants between the ages of 12 and 16 years will also receive a letter with information and will be asked for permission. Each participant can individually start with the intervention whenever they are ready. After inclusion and obtaining informed consent, participants will have one week to complete the baseline questionnaires (T1). Once they completed the baseline questionnaires, the randomization procedure will start. Participants will be randomly allocated to the intervention or waiting-list control groups. The Castor EDC will be used as a random-number generator. A 1:1 allocation ratio will be applied. We utilize block randomization with varying block sizes for this purpose, stratifying for the following variables: gender (boy, girl), type of trauma (physical violence, sexual abuse), and frequency of trauma (single occurrence, multiple occurrences) to ensure that the number of participants is well balanced across both treatment arms within each stratum. Randomization results will be communicated to the participants and their parents (or legal caretakers) via e-mail or phone calls. After the randomization procedure, participants will receive login codes on a website where they can engage in the online psychoeducation programme. The website is available through a login, which allows the research team to evaluate the parts of the website that have been visited and the time spent on the webpage. After two weeks, measurements will be taken (T2) for both groups. After T2, the participants referred to the waiting-list control group will receive access to the online psychoeducation programme. Two weeks after access, post-intervention measurements will be conducted (T3) for the waiting-list control group. Completing the questionnaires takes approximately 15–30 min per assessment. There are no costs incurred by the participants. Participants who dropout before the start of the intervention from the study will be replaced by new participants, with a maximum of 20% of all participants. Participants who dropout during the intervention will not be replaced.

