### Data analyses

2.7.

The G*Power programme (version 3.1.9.2) was used to calculate the sample size. An a priori power calculation showed that the proposed RCT sample required 34 participants (*n* = 17 for each condition). Calculations in G*Power (Cohen’s *d* = 0.5; equivalent of *f* = 0.25 ANOVA) showed that a sample size of *n* = 17 for each group had sufficient power (80%) to reject our null hypothesis, namely, that there was no difference between the two conditions. A between groups effect size of Cohen’s *d* of 0.50 is considered a medium effect size. In a comparable study (Boulton & Boulton, 2017), the between group pre–post effect size on self-blame was very large (*d* > 1.2) and the sample size was also comparable. Based on this study, we believe that the expected effect size (Cohen’s *d*) of .50 in our study is reasonable.

Data will be analyzed using SPSS V.24.0 for Windows (SPSS Incorporated). Descriptive statistics will be calculated for the baseline characteristics of the study population. Parametric data are presented as means with standard deviations (SD), and nonparametric distributed variables as medians with Inter Quartile Ranges (IQRs). The intervention effect will be evaluated for group differences between Condition 1 (intervention) and Condition 2 (waiting-list control group). The primary outcome measure is feelings of shame and guilt, as measured with the SGATS. We will use a will be tested using an two-way repeated measures ANOVA test to determine whether any change in response to the SGATS (i.e. the dependent variable) is the result of interaction between the ‘type of treatment’ (i.e. the waiting-list control group or Intervention group, which is one of our two factors) and ‘time’ (i.e. our second factor T1 and T2). Statistical significance was set at *P* < .05. The secondary outcome measures included the severity of posttraumatic cognition symptoms, posttraumatic stress symptoms, anxiety, mood symptoms, and changes in motivation for trauma-focused treatment and disclosure. Changes between the groups at pre-test and post-test will be tested using ANOVA, while correcting for multiple testing.

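### Randomisation is stratified by gender, trauma type and trauma frequency, but the stated analysis ignores these factors, and the two trauma-type levels do not cover a participant with both

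*Protocol article*

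**What the plan says.** Procedure (2.4): "A 1:1 allocation ratio will be applied", in blocks whose size varies. The scheme works by "stratifying for the following variables: gender (boy, girl), type of trauma (physical violence, sexual abuse), and frequency of trauma (single occurrence, multiple occurrences". The stated aim is "to ensure that the number of participants is well balanced across both treatment arms within each stratum".

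Data analyses (2.7): the primary test is a two-way repeated-measures ANOVA of SGATS. The arm variable is described as "one of our two factors) and ‘time’ (i.e. our second factor T1 and T2" being the other, so the model is closed at two factors. Secondary outcomes are compared between groups by ANOVA with a multiplicity correction, and no covariate or stratification factor is named. On size, "the proposed RCT sample required 34 participants", at an effect "equivalent of *f* = 0.25 ANOVA", which "had sufficient power (80%) to reject our null hypothesis".

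Participants (2.3) admits adolescents with one or more qualifying events. The CTSQ section (2.6.1) screens on two event items joined by and/or, so one person can be positive on both.

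**The concern.** Stratifying tends to align the arms on the three factors, which makes the difference between arms less variable than it would be under simple randomisation. An analysis that leaves the factors out does not register this. Their variance stays in the error term, the standard error is too large on average, and the test rejects too seldom. The trial then accepts the burden of stratifying without taking the gain in precision. With 34 participants a few points of power are worth having.

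The second matter is the definition of a stratum. The stratum has to be entered at the moment of randomisation and is needed again as a covariate. A participant with both physical violence and sexual abuse is eligible, but the article gives that person no defined level of trauma type.

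**Working it through.** **Inputs from the article.** N = 34, 17 per arm; f = 0.25; alpha 0.05; two arms; two time points; three binary stratification factors, so 2 x 2 x 2 = 8 cells.

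**Assumptions.** T1-T2 correlation rho = 0.5. Block sizes {2,4} or {4,6}. Factor prevalences either 50/50/50% or 20/60/70%. Share of the variance of change explained by the three factors, R2 = 0, 0.1, 0.2 or 0.3. The article gives none of these.

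**1. The plan's own figure.** For the arm-by-time interaction, lambda = f^2 x N x m / (1 - rho) = 0.0625 x 34 x 2 / 0.5 = 8.5. The noncentral F with 1 and 32 degrees of freedom gives power 0.807, and 34 is the smallest even N that reaches 0.80. The stated size is therefore reproduced at rho = 0.5.

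**2. The test on the change scale.** With two time points the interaction test equals a two-sample t-test on T2 minus T1. The design effect in SDs of change is sqrt(4 x lambda / N) = sqrt(4 x 8.5 / 34) = 1.0. Stable differences in level between, say, boys and girls cancel in the change score. Only the part of the factors that predicts change matters.

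**3. Limit under perfect balance.** If the arms were exactly balanced on the factors, the arm difference would have variance proportional to 1 - R2, while the unadjusted error term would still estimate about 1. The type I error is then roughly P(|t32| > 2.037 / sqrt(1 - R2)):
- R2 = 0.1: cut-off 2.147, about 4.0%
- R2 = 0.2: cut-off 2.277, about 3.0%
- R2 = 0.3: cut-off 2.435, about 2.1%

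Real balance is imperfect, so the true values should lie between these and 5%.

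**4. Simulation of the actual scheme.** Stratified permuted blocks, 8 cells, N = 34, 6,000 trials per scenario, with change analysed without and with the three factors as main effects. Figures are rounded over the block and prevalence scenarios.

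| R2 | Type I error, unadjusted | Power, unadjusted | Power, adjusted |
|---|---|---|---|
| 0 | about 5% | about 80-82% | about 79-80% |
| 0.1 | about 4-5% | about 81-82% | about 83% |
| 0.2 | about 3-3.5% | about 82% | about 87-88% |
| 0.3 | about 2-3% | about 83% | about 91% |

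The adjusted type I error is about 5% throughout. The gain is about 1-2, 5 and 8 points at R2 = 0.1, 0.2 and 0.3. The loss at R2 = 0 is about 1-2 points. Any further gain from putting baseline SGATS in an ANCOVA is not counted here.

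**5. Trauma type.** Eligibility allows one or more events, screening uses two items that can both be positive, and stratification offers physical violence or sexual abuse. The combination of both is admitted by the first two and has no place in the third.

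**The case against.** The strongest reply is that nothing here endangers validity. The error is conservative, there is no bias, and the gain depends on an R2 that no part of the article supports. If the factors do not predict change, adjusting costs a little. All of this stands, and it is why the point is minor. It does not remove the point: the possible gain is larger than the possible loss, and the trial already collects the factors.

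A second reply is that covariates are commonly left to an analysis plan that is not shown. That holds only in part, because 2.7 does not leave the model open; it counts two factors and names both.

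A reader might also infer that 8 cells for 34 people (34 / 8 = 4.25 each) defeat the randomisation, leave the arms unequal, and call for a single stratifier. The documents do not support that. Block sizes are not given. Under the assumed blocks the arms differ on average by only 1.6-2.3 people, against 4.6 under simple randomisation. A 15 versus 19 split lowers power at the design effect only from 80.7% to 80.2%. Balance inside individual small cells will often be rough, but how many stratifiers to keep is a trade-off on which statisticians differ.

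Nor does the article show that participants with both trauma types are placed case by case. A coding rule may exist in the full protocol or in the Castor set-up. What can be said is that the two levels as published do not cover them.

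**Conclusion.** The point holds as a minor one. The analysis in 2.7 omits the factors that 2.4 stratifies by, so the primary test is conservative to the extent that those factors predict change in SGATS. The cost of the omission is about 1-2, 5 or 8 points of power at R2 = 0.1, 0.2 or 0.3, and adjustment would cost about 1-2 points at R2 = 0. These sizes rest on rho = 0.5, the assumed R2 values, and the assumed block sizes and prevalences; the direction does not depend on the exact values. It would be wrong to read this as an inflated false-positive rate or as invalid randomisation. The gap in the trauma-type levels is real on the text but secondary.

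**What to change.** In 2.7, analyse the T2 score by ANCOVA with baseline score, arm, gender, trauma type and trauma frequency, for SGATS and likewise for the secondary outcomes. If the repeated-measures ANOVA is kept, enter the three factors as factor-by-time terms. Adding them only as between-subject main effects leaves the arm-by-time test unchanged.

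In 2.4, define trauma type with mutually exclusive levels, for example any sexual violence or abuse versus physical violence only, and state the rule for participants with both. If such a rule already exists elsewhere, cite it.

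The cost is a short change of model in 2.7, three degrees of freedom for the factors (plus one for baseline if ANCOVA is used), and one definition in the randomisation set-up. No extra data are needed, and the three stratifiers can stay.
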